**8.2 How to Take Vaginal Samples**

**The Vaginal pH.:** Vaginal pH will be measured using the pHem-Alert indicator (Gynex, Wyoming, USA) according to the manufactures instructions.

**Swabs for multiplex immunologic analysis, bacterial DNA extraction, microarray analysis, metabolomic analysis, and Nugent Score.** Using a speculum the mid lateral vaginal wall is made visible, samples will be collected by the physician or nurse as follows: the swab or cytobrush will be gently pressed against the left mid lateral wall and rolled a total of two full times by twisting the wrist, then the same swabs/cytobrush will sample the right lateral wall.

- (i) The first Dacron swab will be streaked across a glass slide for **Nugent scoring** by placing 8µl of sterile water onto a slide and gently rolling the swab on the slide. The swab will then be placed in a dry tube and placed at 4°C (±2°C). This swab will be used in conjunction with the final swab (see (v) below) for bacterial **DNA extraction**.
- (ii) The second Dacron swab will be cut and placed in a 1.5 mL tube dry, and placed immediately in a -20°C (±2°C) freezer for **Multiplex cytokine and chemokine analysis**.
- (iii) The third specimen will be collected with a cytobrush (Cytobrush plus GT, Cooper Surgical Inc. USA). After sampling both lateral walls, the cytobrush will be placed in a dry tube and placed at 4°C (±2°C) for **metabolomics analysis**.
- (iv) The fourth specimen will also be collected with a cytobrush. After sampling both lateral walls, the cytobrush will be swirled around in a 1.5 ml RNase-free microtube containing RNA stabilization solution. The samples will be placed immediately in a refrigerator at 4°C (±2°C) for **microarray processing**. These samples can be retained in the refrigerator for 24 hours.
- (v) A final swab (Dacron) will be collected and placed in a dry tube and placed at 4°C (±2°C), or on ice, and transported to the laboratory for plating on MRS agar and semi-quantitative analysis of Lactobacilli and **bacterial DNA extraction**.

**8.3 How to Insert Capsule**

In order to properly administer the INHP, the study subject should be instructed to wash their hands carefully with soap and water before commencing. Then using their index finger, the

capsule should be gently inserted into the vagina as far as comfortable and to then lie in a horizontal position for 15 minutes. Wash hands with soap and water when completed.

## **9 INVESTIGATIONAL NATURAL HEALTH PRODUCT**

### **9.1 Supply**

The INHP will be supplied upon study initiation by the study sponsor.

### **9.2 Packaging**

Both the probiotic and the placebo capsules are packaged in identical canisters with a desiccant. Each canister contains 30 capsules.

### **9.3 INHP Capsule Formulation**

Blends of the two strains GR-1® and RC-14® are, together with excipients, formulated into a capsule containing 180 mg of powder, 10 mg of *L. rhamnosus* GR-1® and 41 mg of *L. reuteri* RC-14®. This composition is formulated to contain a minimum of 5 billion ( $5.0 \times 10^9$ ) CFU per dose (capsule), with equal numbers of the two strains; i.e.  $2.5 \times 10^9$  CFU of each of GR-1® and RC-14® at the time of manufacture. The capsules are guaranteed to contain a minimum combined total of  $1 \times 10^9$  CFU throughout their shelf life.

### **9.4 Placebo Formulation**

The composition of the gelatin capsule is 98% Gelatin and 2% Titanium dioxide. The contents of the capsule include glucose, potato starch, cellulose, and magnesium stearate.

### **9.5 Labelling**

In order to maintain the double blind, bottles will be labelled as “J” or “K”. Each bottle will contain either GR-1® and RC-14® or placebo.

Each container will be labelled (in English and French) according to the requirements of the Natural Health Products Directorate and ICH GCP Guidelines and will include:

- Brand name or code of the Natural Health Product (NHP)/Placebo;
- A statement indicating that the NHP is an investigational NHP to be used only by a Qualified Investigator;
- The initials and subject's identifying number;
- The expiration date;
- The recommended storage conditions;
- The lot number;
- The name and address of the manufacturer and Sponsor; and
- The protocol number.

In addition, written instructions on how to administer the INHP will be provided to the subjects.

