**KEY:**

- Subjects with a Nugent Score of 4-6 will be given six (6) capsules to be inserted vaginally twice per day for the next three (3) days. Subjects with a Nugent Score of 7-10 will be treated for BV as appropriate and discontinued from the study. Subjects with a Nugent Score of 0-3 should return in one week to have the Nugent Score reassessed.
- Subjects with a Nugent Score of 4-6 will be given six (6) capsules to be inserted vaginally twice per day for the next three (3) days. Subjects with a Nugent Score of 7-10 will be treated for BV as appropriate and discontinued from the study. Subjects with a Nugent Score of 0-3 will be discontinued from treatment but will be followed until day 129.
- Swabs for microbiota analysis will also be used to assess colonization by probiotic strains on Visits 6, 8, and 9. Microbiota analysis will not be performed at Visit 9.
- Subjects who are not colonized with the probiotic strains at Visit 8 are not required to attend Visit 9, but will receive monthly AE telephone monitoring.

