## **6 STUDY DESIGN**

The study population will consist of post-menopausal subjects presenting with intermediate Nugent Scores (4-6). The study duration is 47 days with a final follow-up at 129 days. A total of fourteen (14) subjects will be randomized into this exploratory study.

Subjects will undergo the following treatment phases:

- Two weeks of no treatment (Days 1-15); followed by
- Three days in which each subject randomly receives either two intravaginal placebo capsules or two intravaginal probiotic capsules (Days 16-18) each day; followed by
- 18 day wash-out period; followed by
- Three days in which each subject randomly receives either two intravaginal placebo capsules or two intravaginal probiotic capsules (Days 37-39) each day; and
- Follow-up approximately 90 days after last treatment.

The capsules given on Days 37-39 will not be the same as the capsules given on Days 16-18. During one treatment period the probiotic will be given and during the other treatment period, placebo will be given. Not the subject nor the study staff will know which capsules contain the probiotics.

INHP (placebo or probiotic) consists of capsules to be administered vaginally on study treatment days; once in the morning and once in the evening approximately 12 hours apart.

Following the first two weeks of no treatment, subjects will be given six (6) placebo or probiotic capsules, on Day 15, to be administered vaginally twice daily for 3 consecutive days. Panty liners will be given to use on treatment days. On Day 36, subjects will again be given six (6) placebo or probiotic treatment capsules to be administered vaginally twice daily for

3 consecutive days in the same manner. A diary to track compliance and to rate general vaginal discomfort and record any other adverse events will be given to the patients and reviewed by the study Investigator or designee at the following visit. Subjects that remain colonized with the probiotic strains at Day 47 will return for a follow-up visit on Day 129. During the follow-up phase, all subjects who received treatment will be queried monthly via telephone regarding adverse events on a monthly basis until Day 129. See Section 8 for visit details.

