## **7.2 Randomization Process**

Subjects screened in this study will be sequentially granted a three digit study number. For each study number a randomization envelope is supplied indicating the treatment assigned for both Treatment Phase I and Treatment Phase II. Treatment should be given in the order listed in the randomization envelop. The bottles are labelled as “J” and “K” from the supplier who knows the content of each bottle. Study staff and study subjects will be blinded as to study treatment being given: the probiotics or placebo.

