#### **Treatment Phase II - Visit 6 – Day 36 (+/-2 days)**

The following assessments will be performed:

- Subjects will be queried regarding any adverse events they may have experienced;
- A vaginal health questionnaire will be completed;
- Five (5) vaginal samples and a vaginal pH measurement will be taken in the same manner as described for Visit 2;

- Subjects that have a Nugent Score of 4 – 6 will then be given either six (6) placebo or six (6) probiotic capsules per the randomization and will be instructed to administer them vaginally two (2) times daily for the next 3 consecutive days. Written instructions for product administration will be provided. Panty liners will be supplied to use on treatment days;
- Subjects will be instructed to keep the capsules in the container and refrigerated until use;
- Subjects will be given a diary to track compliance and to rate any general vaginal discomfort and record any other adverse events;
- Review concomitant medications; and
- An appointment will be scheduled to return in 4 days (5 days is acceptable) for Day 40 visit.

*Subjects with a Nugent Score of 7 – 10 at Visit 6 will be treated for BV as appropriate by the Investigator and discontinued from the study. End of treatment assessments and procedures (Visit 8) should be done.*

*Subjects with a Nugent Score of 0 – 3 at Visit 6 will be discontinued from treatment. If these subjects are still colonized with at least one of the probiotic strains they will return for a final study visit on Day 129. All subjects discontinued from treatment will be queried via telephone regarding adverse events on a monthly basis until Day 129.*

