**Visit 9 – Day 129 (+/-7 days) Additional Follow-Up**

Subjects who are still colonized with at least one of the probiotic strains at Visit 8 (or at Visit 6 if they discontinued treatment at that time) will return for a final study visit. The following assessments will be performed:

- Subject will be queried regarding any adverse events they may have experienced; and
- One (1) vaginal swab will be taken in the same manner as the microbiota swab described in Section 8.2. This swab will not be used to perform the microbiota analysis however; the swab will only be used to determine whether the subject continues to be colonized by the probiotic.

Follow-up will be conducted for all treated subjects (including those that were discontinued). All treated subjects will be queried via telephone regarding adverse events on a monthly basis until Day 129.

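### Two shared bottle letters, and a strain result the site must act on, leave the blind exposed: one positive Visit 6 result could reveal all 14 women's allocation

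*Protocol*

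**What the plan says.** The study is described as double-blind. The synopsis names the subjects and the investigator as blinded, and Section 7.2 adds the study staff.

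**Coding.** Section 9.5: "In order to maintain the double blind, bottles will be labelled as “J” or “K". Section 7.2 says where the letters come from: "The bottles are labelled as “J” and “K” from the supplier who knows the content of each bottle". The same section says what the site holds: "For each study number a randomization envelope is supplied indicating the treatment assigned for both Treatment Phase I and Treatment Phase II". Section 6 ties the phases together: "During one treatment period the probiotic will be given and during the other treatment period, placebo will be given".

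**Strain results.** The key to the visit schedule in Section 2 says: "Swabs for microbiota analysis will also be used to assess colonization by probiotic strains on Visits 6, 8, and 9". Section 8.1, on women who reach Visit 6 with a Nugent Score of 0 to 3 and stop treatment, says: "If these subjects are still colonized with at least one of the probiotic strains they will return for a final study visit on Day 129". The Visit 9 text applies the same rule to the Visit 8 result for the other women. Women found not colonised at Visit 8 need not attend Visit 9 and are only telephoned.

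The protocol does not say who receives the strain results, when they arrive, or that any blinded person is kept from seeing them.

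**The concern.** Each arrangement is tolerable alone; the difficulty is the combination. With two letters for the whole trial, learning what one letter means for one woman gives its meaning for all of them, and the envelopes supply every woman's order. A strain result is close to a direct reading of which product a woman received, and the site must have it, at least as a yes or no, to schedule Visit 9. The Day 129 appointment itself discloses the result to staff and to the woman.

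If the code became known while women were still under assessment, symptom ratings, the investigator's judgement of adverse event causality and possibly the Nugent reading would be open to bias. A trial of this size has little tolerance for that. If McNemar's test is done in its exact form (an assumption; the protocol names only the test), six discordant pairs all in one direction give p = 2 × 0.5^6 = 0.031, and five give p = 2 × 0.5^5 = 0.0625. One shifted reading could move the primary result across 5%.

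**Working it through.** The plan states no figure to reproduce, so the check is one of logic, with a few counts.

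**Inputs.** 14 women randomised (Section 13.2); two phases each, one probiotic and one placebo (Section 6); capsules on Days 16–18 and 37–39 (Section 6); strain assessment at Visits 6, 8 and 9, nominally Days 36, 47 and 129 (Section 2).

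**Step 1: reach of a decoded letter.** 14 × 2 = 28 subject-phases share 2 codes. If one letter is decoded, the allocation of 28 of 28 can be read from the envelopes. With a separate code for each woman and phase, the same result reveals 1 × 2 = 2 of 28.

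**Step 2: Visit 6.** The swab is taken before any Phase II capsule, 36 − 18 = 18 days after the last Phase I dose. A positive can come only from the Phase I bottle, natural carriage or a false positive apart. Let q be the chance of a positive if probiotic came first and f the chance if it did not, with either order equally likely beforehand. The probability that the Phase I letter is the probiotic is then q/(q + f). Neither value is in the protocol. For q from 0.1 to 0.5:

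- f = 0: 1.00
- f = 0.01: 0.91 to 0.98
- f = 0.05: 0.67 to 0.91

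**Step 3: Visit 8.** The swab is 47 − 39 = 8 days after the last Phase II dose and 47 − 18 = 29 days after the last Phase I dose, so carry-over from Phase I competes as an explanation. Assume colonisation of 0.3 to 0.5 at 8 days and 0 to 0.10 at 29 days. The probability that Phase II was probiotic is at least 0.3/(0.3 + 0.10) = 0.75, and 1.00 with no carry-over. One result is therefore suggestive. Three consistent, independent results at the least favourable ratio, 0.3/0.10 = 3, give 27/(27 + 1) = 0.96, so several would in practice settle the code.

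**Step 4: how likely a Visit 6 positive is.** Assume 7 women receive probiotic first (the split is not stated). The chance of at least one positive is 1 − (1 − q)^7:

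| q (assumed) | Chance of at least one |
|---|---|
| 0.05 | 30% |
| 0.10 | 52% |
| 0.20 | 79% |
| 0.30 | 92% |
| 0.50 | 99% |

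This is the chance that such a result exists. The site is made to act on a Visit 6 result only for women with a Nugent Score of 0 to 3 at that visit, so the chance of a forced disclosure is lower. Section 5.3.2.2 reports gradual decline of the strains, with none detectable 30 days after oral dosing stops. That makes some detection at 18 days credible but gives no value for q.

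**Step 5: timing.** The decision concerns Day 129, which is 129 − 36 = 93 days after Visit 6 and 129 − 47 = 82 days after Visit 8. The schedule allows late reporting but does not require it.

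**The case against.** The strongest reply is that nothing shows the blind would fail in practice. The strain result is needed only for a visit about three months later. If the laboratory reported after the last woman's Day 47, efficacy data would be almost untouched. The decisive case is also narrow: a woman given probiotic first, still colonised 18 days later, with a Nugent Score of 0 to 3 at Visit 6. Her own Phase I assessments are then complete and she has no Phase II. Phases finished before a result arrives were assessed blind, so 28 decoded allocations are not 28 biased observations. The protocol does not say who reads the slides or whether they see letters or strain results. It is also a small exploratory pilot.

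All of that stands, and it limits the size of the point. A reader might infer that any single colonisation result unblinds every woman, or that the Visit 9 rule breaks the blind while later women are being treated. The documents support neither. A lone Visit 8 positive may be carry-over, and the 30-day figure in Section 5.3.2.2 that would argue against this concerns oral use. The second inference needs both early reporting and staggered enrolment, and neither is stated.

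Two further readings are natural but unwritten: that each letter means the same product for every woman, and that the envelope lists letters. On the second, an envelope naming the product would defeat the stated blinding outright.

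The objection does not remove the exposure. No passage delays or restricts the results, and the subject number on the label does not help while the letter is shared.

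**Conclusion.** The point holds as a blinding vulnerability created by two stated rules, not as a demonstrated break. Given a common meaning of the letters and no natural carriage, one positive Visit 6 result identifies the probiotic letter and could reveal the allocation of all 14 women, up to 28 subject-phases. One Visit 8 positive is suggestive; several consistent ones would settle the code. Bias in efficacy data would arise only for assessments made after results reach the site, and the protocol leaves that timing open. The matter deserves correction before enrolment because the labelling and the rule that sends strain results to the site are both fixed in the protocol, and an analysis plan cannot repair them.

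**What to change.** **Sections 7.2 and 9.5.** Replace J and K with a unique code for each woman and phase, and have the envelopes list only those codes. The lot number that Section 9.5 puts on each label should not separate the two products, or it becomes another shared code.

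**Section 8.1.** State that the laboratory keeps strain results from site staff and slide readers and releases only the yes/no decision on Visit 9. Release should follow the woman's last efficacy assessment (Visit 8, or Visit 6 if she stopped treatment then), and preferably the last woman's Day 47, as far as the Day 129 window allows. All other strain data stay withheld until database lock. The yes/no still discloses that woman's colonisation status, but with unique codes it reveals at most her own two phases, after her efficacy data are complete.

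**Cost.** Relabelling, and possibly repackaging, into about 14 × 2 = 28 containers: Section 9.2 describes canisters of 30 capsules, while six are dispensed per phase. One laboratory instruction is also needed. No visits are added and no treatment rule changes.

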## **9.6 Storage**

The Investigator or designee will be responsible for ensuring that all INHP is adequately accounted for and kept in a secured area accessible only to individuals authorized to dispense the product. The capsules should be kept refrigerated at the site at 4-6°C ( $\pm 2^{\circ}\text{C}$ ) for the duration of the study to ensure optimal stability. Once dispensed to subjects, subjects are encouraged to keep the INHP refrigerated; however, this is not a requirement. Subjects will be instructed to keep the INHP from being exposed to severe heat (e.g. a parked car on a hot day).

## **9.7 Accountability**

All INHP provided by the Sponsor for the study and that is given to a subject must be accounted for in writing. The Investigator or designee must document receipt of all INHP at the site, inventory at the site, use by each subject, and the return of all INHP supplies to the Sponsor. These records should include dates, quantities and batch/lot/serial numbers of the INHP assigned to the subjects.

The sites must remind the subjects to return treatment containers that were dispensed for the purpose of INHP accountability. All returned containers (used and unused) may not be dispensed to another subject.

All INHP containers (used and unused) and corresponding accountability forms must be returned to the Sponsor at the end of the study.

## **9.8 Subject Compliance**

Subject compliance that is not 100% must be properly documented. Any temporary or permanent discontinuations in INHP must be reported, specifying the date and time of missed administrations, the date of re-administration and the reason for discontinuation. Proper instructions on how to insert the INHP must be given to each subject as often as needed.

Subjects should be instructed to take the INHP at the same times twice daily, once in the morning and once in the evening at about 12 hour dose interval. If a dose is missed, that dose should be taken as soon as possible provided it is taken at least 6 hours prior to the following scheduled dose time. If more than two doses are missed, the subject will be discontinued from the study.

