## 12 SUBJECT WITHDRAWAL

Subjects have the right to withdraw from the study at any time and for any reason. In the event that a subject withdraws, every effort must be made to obtain "End-of-Treatment" information by completing, within the shortest delay, the assessments and procedures planned at Visit 8 – Day 47. The reason(s) for withdrawal must be described, and if more than one is given, the Investigator must specify the primary reason.

The Investigator will maintain the subject in the study as long as possible. However, the Investigator may also decide to withdraw a subject from the study in any of the following circumstances apply:

- Subject no longer meets the inclusion or exclusion criteria;
- Nugent Score less than three (3) or greater than six (6);
- Occurrence of an adverse event for which, in the opinion of the Investigator, the continuation of the study may compromise the safety of the subject; and
- Pregnancy.

In the case of withdrawal due to an adverse event which may potentially be related to the investigational products, the subject should be followed up until all abnormalities return to acceptable levels or stabilize. All adverse events must be documented on the corresponding pages in the case report form.

Any premature termination of treatment must be reported immediately to the Sponsor's designated representative.

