#### **13.1.1 Analysis Populations**

**Safety Set:** All randomized subjects who received the INHP at any dose or placebo, will be included in the safety analyses.

**Full Analysis Set:** All randomized subjects will be analyzed following the principle of intention-to-treat (ITT) provided they received the INHP or placebo and had at least one efficacy observation after first insertion.

**Per protocol Set:** All subjects who are compliant with the study protocol (i.e., who do not experience any major protocol deviations), who received the INHP or placebo and had at least one efficacy observation after first insertion.

The primary efficacy analysis will be based on the Full Analysis Set, although a secondary analysis will also be performed based upon the Per-Protocol Set (if there are differences) to assess the sensitivity of the analysis to the choice of analysis population.

The analyses of all other efficacy endpoints will be based upon the Full Analysis Set only. All safety analyses will be based upon the Safety Set.

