##### **13.1.2.1 Nugent Score Analysis**

$$H_0: \pi_A = \pi_P$$

$$H_a: \pi_A \neq \pi_P$$

$\pi_A$  denotes proportion of subjects used intravaginal probiotic capsules had shown improvement in Nugent Score from intermediate (4-6) to normal status (0-3)

$\pi_P$  denotes proportion of subjects used intravaginal placebo capsules had shown improvement in Nugent Score from intermediate (4-6) to normal status (0-3)

McNemar's test will be utilized to test the hypothesis at 5% level of significance, 2-sided.

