## **13.2 Sample Size and Power Considerations**

No formal sample size calculation was performed for this study. The number of subjects to be randomized is based on feasibility and practical considerations for such an exploratory study. It is planned that a total of fourteen (14) subjects will be randomized in this study.

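### Section 9.8 ends study participation, not only capsule use, after more than two missed doses, so scheduled outcomes are lost from a paired analysis that is meant to follow intention-to-treat

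*Protocol*

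**What the plan says.** Protocol Section 9.8 (Subject Compliance) sets the rule: "If more than two doses are missed, the subject will be discontinued from the study".

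Section 13.1.1 (Analysis Populations) defines the Full Analysis Set: "All randomized subjects will be analyzed following the principle of intention-to-treat (ITT) provided they received the INHP or placebo". A further condition is that each woman has an efficacy result from some point after she began the capsules. The section adds: "The primary efficacy analysis will be based on the Full Analysis Set". A Per Protocol Set, restricted to women without major deviations, serves as a sensitivity analysis.

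Section 13.1.2.1 gives the primary test: "McNemar's test will be utilized to test the hypothesis at 5% level of significance, 2-sided". The design is a crossover in which each woman has one probiotic and one placebo period of six capsules. Section 13.2 fixes the size: "It is planned that a total of fourteen (14) subjects will be randomized in this study".

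Section 12 (Subject Withdrawal) tells the investigator to keep women in the study as long as possible, and its list of withdrawal circumstances does not name missed doses. When a woman does withdraw, the site should try to gather final data by "completing, within the shortest delay, the assessments and procedures planned at Visit 8". Section 8.1 (Visit 9) keeps monthly adverse-event calls for all treated women, including those discontinued.

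**The concern.** Adherence is handled in two incompatible ways. Section 13.1.1 handles it by analysis set: everyone treated and observed is in the primary set, and major deviators leave only the Per Protocol Set. Section 9.8 handles it by ending participation after randomisation, so later outcomes are never collected. Missed capsules may reflect discomfort or a reaction to the product, so the missing outcomes may be informative.

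The test is paired and the trial has at most 14 pairs. A missing or off-schedule result in either period weakens that woman's contribution to the comparison. A SAP can choose how to treat missing results, but it cannot recover swabs that the protocol stopped taking.

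**Working it through.** **1. Can Section 9.8 be read as stopping capsules only?** No. The protocol separates the two ideas elsewhere. The key to the Study Visit Schedule and the Visit 6 text in Section 8.1 take women scoring 0-3 at Visit 6 off treatment while continuing to follow them. The Visit 3 and Visit 6 texts use discontinuation from the study for scores of 7-10. Section 9.8 itself mentions temporary or permanent discontinuation of the product before switching to the study.

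**2. Which outcomes are lost?** The diary that tracks compliance is reviewed at Visit 4 (Day 19) and Visit 7 (Day 40), where a Nugent swab is also taken.

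| Removal found at | Last capsule day | Day of this swab | Scheduled one-week sample | Later outcomes |
|---|---|---|---|---|
| Visit 4 (Phase I) | 18 | 19 (1 day after) | Day 26 (8 days after), lost | Days 36, 40, 47 lost |
| Visit 7 (Phase II) | 39 | 40 (1 day after) | Day 47 (8 days after), may be lost | none further for Nugent score |

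The primary objective (Section 6.1) concerns a normal state kept for one week. The Section 12 fallback is taken as soon as possible. If it follows a Day 19 or Day 40 discovery, it falls up to about a week before the scheduled sample. It cannot supply a second period that never took place. The follow-up calls, and the Day 129 colonisation swab for some women, yield no Nugent score.

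**3. Does she leave the Full Analysis Set?** Normally not. One post-insertion score is enough, and the Day 19 swab provides it.

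**4. How much can one pair matter?** The plan states no power or effect size, so there is no figure to reproduce. With b discordant pairs favouring one product and c the other:

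- Exact two-sided McNemar, all b pairs one way: p = 2 × 0.5^b. For 6-0, 2/64 = 0.031. For 5-0, 2/32 = 0.0625.
- Loss of an unfavourable pair works the other way: 6-1 gives 2 × (7+1)/128 = 0.125, and 6-0 gives 0.031.
- Uncorrected McNemar: (b−c)²/(b+c) against 3.84. For 5-0, 25/5 = 5.0 (p=0.025), still below 5%. Its own boundary is lower: 4-0 gives 16/4 = 4.0, and 3-0 gives 9/3 = 3.0.

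Section 13.1.2.1 does not say which version applies.

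**5. How likely is a loss?** No rate is given. For an assumed probability q that a woman meets the rule, the chance that at least one of 14 does is 1 − (1−q)^14: 25% at q=2%, 51% at 5%, 77% at 10%. A shift like those in step 4 also needs the lost pair to be discordant. If half are (assumed), replace q by q/2: 13%, 30% and 51%. The result must also lie at the significance boundary.

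**The case against.** The strongest reply is that the harm is easily overstated, and much of that stands.

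- A reader might infer that these women drop out of the Full Analysis Set and that it becomes nearly a per-protocol set. The documents do not support this. Section 13.1.1 keeps any treated woman with one post-insertion score, and the Per Protocol Set also excludes every other major deviation, so the sensitivity comparison keeps a purpose.
- A reader might infer that every removal deletes a pair. That depends on missing-data handling, which a SAP may settle. Counting missing as not improved, for example, keeps the pair in the table. A Phase II removal also keeps her Phase I result.
- It might seem that an early swab can never serve as the primary outcome. The one-week horizon is in the objective, but Section 13.1.2.1 names no visit, so this is open.
- The course lasts three days. If the rule counts per period, a woman must miss at least three of six capsules. If it counts over both periods, it is three of twelve. Section 9.8 does not say which.
- Other rules also cost pairs: a score of 0-3 at Visit 6 stops treatment, and scores of 7-10 or antibiotic use end participation. Missed doses may be the smaller route.
- This is a 14-woman exploratory pilot sized on feasibility, with no power claim.

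What survives is the conflict itself. Section 9.8 stops collection of outcomes that the declared analysis principle would use, and Section 12 points the other way.

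**Conclusion.** The point holds as an internal conflict between Sections 9.8, 12 and 13.1.1 with a limited consequence. A Phase I removal certainly loses the scheduled Day 26 sample and all Phase II outcomes. A Phase II removal may lose the Day 47 sample. The woman usually remains in the Full Analysis Set with an incomplete or off-schedule pair, for a reason that may relate to tolerability.

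In a trial of at most 14 pairs, a single lost discordant pair can change the conclusion, in either direction. The 6-0 to 5-0 illustration rests on the exact test and a result already at the boundary; the uncorrected test does not cross 5% at that step. The chances of loss rest on assumed non-adherence rates and are not forecasts: a reader should not take 51% or 77% as the probability that the trial's result flips. The change is worth making because it is cheap and the outcomes cannot be recovered later. Nothing here bears on whether the dose threshold itself is right.

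**What to change.** Reconcile Sections 9.8, 12 and 13.1.1 by separating stopping the product from leaving the study. Whatever treatment rule the sponsor keeps for missed doses:

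- continue the already scheduled samples and visits in both phases for these women, unless they withdraw themselves;
- analyse them as randomised in the Full Analysis Set;
- exclude them only from the Per Protocol Set;
- say in Section 9.8 whether missed doses are counted per period or over both.

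The cost is wording in those sections and completion of visits that are already planned. If the product is stopped in Phase I, the Phase II score is an as-randomised outcome without treatment, so some dilution of the effect in the Full Analysis Set is the price. The change does not recover pairs lost through the Nugent 0-3, Nugent 7-10 or antibiotic rules.
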